## Abstract

**Background:**

MINI SALTEN is a program developed to increase moderate to vigorous physical activity (PA) and improve eating habits at home and school in first grade children. It aims to assess the effects of a technology family-based and PA school-based intervention. The purpose of this manuscript is to describe the protocol design and the MINISALTEN intervention.

**Methods:**

This is cluster-randomized controlled trial designed to run from July 2015 to November 2016 in 12 public schools of the city of Buenos Aires, matched for socio-demographic characteristics. The intervention is based on two main components: (a) “active breaks” (AB): implemented during school breaks by a PA instructor; (b) “virtual” (V): web-based contents delivered to the families via a multiplatform application. Using a computer generated random sequence participants are allocated to one of four intervention conditions: (AB), (V), (AB + V), and control (C). Outcomes are measured at baseline and 12 months post intervention, and will include data collected from the child and her/his mother/father or guardian. Primary outcome measures are: PA and sedentary behaviour (measured with accelerometers). Secondary outcome measures related are: percentage of kilocalories (kcal) from added sugars, and from total and saturated fats; grams of fruits and vegetables; and number of snacks and kcal coming from their added sugars and total and saturated fats. Family socio-economic level, home environment, and school environment will also be assessed. Statistical analysis is on an intention-to-treat principle. Baseline characteristics are described using summary measures and mixed models (with school as random effect). The effect of the two interventions will be estimated using a generalized mixed linear model with link and distribution selected according to the type of outcome. Included random effects are: child (or mother/father or guardian) accounting for repeated measures; school accounting for cluster induced by school. The most parsimonious model for each outcome will be reported. The False Discovery Rate criterion will be used to correct for multiple testing in non-planned analyses.

**Discussion:**

It is a pioneer assessment of the impact of a technology-based virtual intervention and a school-based PA program, designed to prevent obesity, and involving the parents at public schools of Buenos Aires.

**Trial registration:**

Current Controlled Trials ISRCTN58093412. Registered March 14th, 2016 (retrospectively registered).

## Background

International studies have demonstrated the effectiveness of interventions aimed at improving lifestyle behaviours with the goal of preventing body weight gain and/or improving healthy habits, hence contributing to avoid non-communicable chronic diseases. Nevertheless, most studies represented in the current literature come from developed countries and have been carried out in school settings [1]. In Argentina there is a lack of evidence regarding the effectiveness of physical activity (PA) and healthy eating (HE) habit interventions targeting young school children and their parents in randomized controlled trials using both objective and subjective (questionnaires) methods.

Physical activity during young childhood has been favourably associated to health outcomes regarding cardiovascular risk factors [2–4], body composition [5–7], motor skill development [8, 9], and psychosocial characteristics [10]. Current guidelines recommend that preschool children practice no less than 15 min per hour of at least light intensity physical activity while they are in childcare [11]. By age 6, the recommendation is 60 min each day. For Argentine children, commencement of first grade represents a drastic shift from a kindergarten environment devoid of tables and chairs, in which they freely wander around, to a classroom where they are expected to remain seated at their desk. A complete school day typically goes from 8:30 am to 4:00 p.m.; PA class is bi-weekly (60 min each), breaks are every 45 min (5–10 min each), and playground space is very variable. The level of PA practiced during school hours has been scarcely researched. Moreover, eating habits in school children and their impact on health has been also under-researched, especially in Latin American countries undergoing a process of nutritional transition [12–14].

A direct antecedent to the current study is an intervention that proved successful at improving core dietary behaviours and attitudes, in 10**–**12 year old children attending public schools of the province of Buenos Aires [15, 16]. The alarming obesity prevalence found in this population (21.6%) and previous data on Argentine children [17, 18], indicates that prevention is probably furthered if it commences at an earlier age and involves the parents to promote long-term sustainment of the proposed goals. Argentina is not exempt from the ostensible increase in recent years in the use of smartphones and tablets and evidence indicates that communication based on these new technologies has a strong potential to improve healthcare and clinical interventions in the community [19–21]. However, few of these tools have been validated and there is scarce evidence of their effectiveness regarding health outcomes [22]. Even fewer studies have explored the success of such applications at improving eating habits and at increasing PA [23, 24].

MINI SALTEN (More Jumping and Better Eating at Home and School) is a technology and school-based multicomponent intervention developed to increase moderate to vigorous PA at school and at home and also improve eating habits in first grade children. Evidence from international settings indicates that targeting parental involvement in addition to nutrition and physical activity in the school setting is an important determinant for the success of school-based interventions [25]. The purpose of this manuscript is to describe the protocol design and the MINI SALTEN intervention. The main aim of MINI SALTEN is to assess the effects of a technology family-based and PA school-based intervention on (1) physical activity, and (2) quality of diet and eating behaviour in first grade children of the city of Buenos Aires. The specific aims are to: (a) evaluate the effects of the intervention on children’s specific eating habits (fruit and vegetable consumption, energy intake, snack and breakfast quality), (b) evaluate progression of body mass index (BMI) over time, and (c) identify parental factors associated with changes in PA and in children’s quality of diet. The study hypothesis is that first grade children of public schools of Buenos Aires are more likely to develop healthy habits related to preventing obesity if they are stimulated to active play during breaks and when their parents and themselves are regularly exposed to educational stimuli, delivered virtually.

## Methods/Design

In April 2015, the Ministry of Education agreed to grant access to public schools of the city of Buenos Aires. The Institutional Review Board of the Argentine Medical Association provided ethical approval on 02/25/2015. Informed parent consent/child assent, congruent with local legislation were sought.

### Study design

This is a cluster-randomized trial with four arms defined by a factorial structure of the two components of the intervention: the school-based (active breaks) (yes/no); family-based (web-based or virtual) (yes/no). The four arms of the study are: Active Breaks (AB) intervention, Virtual intervention (V), Active Breaks and Virtual intervention (AB + V) and neither AB nor V, control (C). The unit of randomisation is the school (rather than individual children/families). The study will run during two school semesters along two calendar years (the second semester of first grade and first semester of second grade). Because the enrolment process of families in the study lasted approximately 3 months, the study ran from July 2015 to November 2016.

### Study population and randomization

The Ministry of Education of the city of Buenos Aires pre-selected a pool of public schools, which were invited to participate. Written invitations and an information pack were sent to each school Principal, followed up with visits to recruit schools. Consent was sought from Principals and first grade teachers. The 12 participating schools are located in middle-to low-income areas of the city. The schools were randomly allocated to one of the four intervention conditions using a computer generated random sequence. Blinding was not possible due to the characteristics of the intervention.

While part of the intervention is school-based, the primary outcomes are measured at subject level. Subjects of the study are first grade children. Mothers are also being assessed to evaluate parental factors; the dyad comprised the child and either parent or guardian in case the mother can’t attend the interview. All parents of first grade students (typically aged 6) of participating schools were invited to attend a meeting in which the nutritionist presented the program and described the study as well as the type of participation expected from parents and children. Those expressing interest were invited to enrol in the study and an initial face-to-face interview to be held at school was scheduled. Dyads were excluded if the child had severe intellectual difficulties or limitations to engage in physical activity, suffered from illnesses compromising nutrition or food selection, was taking medication known to affect body weight; or if the participating adult had severe intellectual difficulties. After screening for eligibility, the interviewer briefly explained the purpose and characteristics of the program and those who agreed to participate signed the informed consent form. Because the study is web-based, families without Internet access (at home, work or in the neighbourhood) are discouraged from participating. Should they still express wish to participate their data is collected but will be excluded from the analysis. Dyads attending a given school were assigned to the intervention condition randomly allocated to that school.

### The intervention

The intervention is framed within the ANGELO (Analysis Grid for Elements Linked to Obesity) ecological model [26], which promotes environmental modifications encompassing the physical, economic, political, and/or socio-cultural realms, especially with regard to what is available, what are the costs, what are the rules, and what are the attitudes and beliefs at play in the adoption of healthier eating and PA habits. When designing the web-based presentations and activities, low cost activities and argentine family customs are taken into account as well as the attitudes and beliefs targeted to encourage behavioural changes (HE and PA) of children and their parents, especially their mothers. Implementation of the protocol is relied on two intertwined pillars: 1-accessibility/ availability (of practicing PA by promoting active breaks) and 2-knowledge/education (delivered by the virtual intervention).

The MINI SALTEN interventions are based on two major components:Virtual (V). Especially designed web-based contents, targeting families and children aimed at 1) encouraging the improvement of eating habits of the whole family both at home and at school, and 2) increasing mothers’ knowledge of the benefits of PA and consequences of sedentary behaviour, and proposing pleasurable movement entailing activities for the children. Thematic goals are: breakfast, PA, water intake, fruit and vegetable consumption, energy balance, parents as models, and snacking. The contents are produced, developed and structured by nutritionists and specialists in education. The technical team of Nearpod, provides advice on the design and technical support for uploading the theoretical units.The material mainly comprised information on the benefits entailed in attaining the proposed goal, tips on how to overcome the particular environmental barriers, and recommendations regarding its implementation (Table 1). This material is delivered through a multiplatform application (https://nearpod.com/) consisting essentially of a personalized virtual campus in which videos and PowerPoint presentations can be shared with the viewer and interactive activities designed to motivate their compliance were proposed. The platform was originally developed as an interactive educational tool, for teachers within the classroom. For the purpose of this research, adaptations are made so that families can receive the presentations on their smartphone, tablet, or computer, and view them during their free time, ideally at home. .Each thematic goal is addressed in 2–5 sequential presentations. Families are expected to interact with 23 presentations during the length of the program. It is important to note that although the web contents target mothers, the rest of the family (parents and siblings) are able (and invited) to access the virtual content.Active Breaks (AB). Activities comprising movement during school breaks are promoted with motivation as a backbone and devoid of a competitive strive; active play in which fun, pleasure, and sharing were emphasized. PA instructor-guided activities take place three times a week during two school breaks with the goal of promoting active play for a minimum of 20–30 min/day, depending on each school. The intervention staff provides, simple, basic, affordable elements to be implemented always during school breaks and in PA class (the latter only if the teacher is willing). All first grade children of the enrolled schools allocated to receive the AB intervention participate in this activity. MINISALTEN developed a blueprint of suggested 15 playful games and activities designed to encourage moderate to vigorous PA for children ages 5–7. The goal is that children spend 75% of their time running or jumping (e.g. running in zigzags while chasing a “mouse”; climbing and crouching imitating animal movements, rope jumping, flying like a fish, etc.). The 6 PA instructors rotate among schools to ensure that any individual facilitator aspect is incorporated to all participating schools. Specific gear, likely to increase the child’s level of PA is provided to this effect. This school-based intervention is complemented with a partial version of the web-based program. Its content dealt with the benefits of being physically active, tips on how to reduce screen time, statistics regarding sedentary behaviour, a description of PA recommended for a child, frequently encountered environmental barriers, and how to overcome them.

**Table 1 Tab1:** Themes and theoretical content of material delivered via the multi-platform application

Theme	Number	Theoretical content
Program presentation	1	Description and purpose/value of MINI SALTEN.
Breakfast	4	Benefits, variety and quantity of food items, barriers, and tips for implementing.
Physical activity	4	Importance of being physically active, recommendations, barriers, and tips for implementation.
Parents as role models	2	Concept illustrated with examples.
Water intake	2	Importance of hydration for the body and how to recognize dehydration.
Energy balance	2	What it is and why it needs to be balanced.
What we eat	1	Food groups, amounts, and examples of healthy menus.
Fruit and vegetables	5	Benefits, tips, recipes, importance of colours, seasonal fruits and vegetables.
Snacks	2	Suggested healthy and affordable snacks for school. Frequency and variety.

*N* number of interactive presentations of each theme

Both energy expenditure and energy intake are crucial components of energy balance [27]. Active breaks at school are a window of opportunity to increase energy expenditure. The virtual web- based program is aimed at instructing the child and family on nutrition with the ultimate goal of improving the other component of the energy equation.

Process evaluation is supervised by a coordinator who monitor attendance and fidelity of implementation of the intervention component delivered by the PA instructors, as well as compliance with the expectation that activities practice during breaks be of moderate to vigorous intensity during 80% of the allocated time. This is ensured through careful planning and daily registry.

The amount of time assigned to this intervention results from the number of school days that are planned for intervention minus the days children do not attend for different reasons (holidays, elections, premises’ disinfection, etc.), or those in which the PA instructors are unable to deliver the intervention for any other reason.

All participant first grade children of the 12 enrolled schools will be assigned to one of the interventions: Active Breaks (AB), Virtual (V), Active Breaks and Virtual (AB + V) and control (C) group. Based on the aforementioned components four types of intervention were designed.

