The efficacy of the intervention will be evaluated through outcomes measured on the children. Primary outcomes: (Aim 1 -PA): 1) Total time (minutes/day) of children’s moderate to vigorous PA and 2) Sedentary time (minutes/day). Secondary outcomes: (Aim 2 - Quality of diet): 1) Percentage of kilocalories (kcal) from added sugars, 2) Percentage of kcal from total fats and saturated fats, 3) Grams of fruits and vegetables, and 4) Number of snacks and kcal from total fats, saturated fats, and sugars coming from snacks. The 4 secondary outcomes will be measured by a 24-h recall, using the multiple pass method, applied to both mother and child and complemented with information regarding school breakfast and lunch in order to collect intake from an ordinary school day, covering both home and school.

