## Discussion

To our knowledge, this is the first study to assess the impact of a communication and technology-based virtual intervention involving the parents of first grade children of public schools in Latin America and designed to prevent obesity in their families. If this resource should prove to be effective, and taking into account the widespread use of new communication technologies, it may contribute to the dissemination and promotion of health related habits, and ultimately aid in the fight against the challenge posed by obesity. The additional value of this tool is that it is amenable to be replicated and implemented at a distance, hence resulting cost effective.

Because all measurements will be obtained according to standard methodology and protocols, particularly the objective measures of PA with accelerometers, an added value of data to be reported by this study is that it is one of the few to provide unbiased information regarding dietary and PA patterns of first grade children of Argentina.

The theoretical model that pervades the program emphasizes accessibility and knowledge as critical pillars of change. The first one is addressed by providing an increased number of opportunities for practicing PA during school breaks; the latter in the provision of knowledge about healthy habits related to food intake and PA. Assessment of a theoretical model in which the components are split off and each one of them is evaluated both separately and then together with an objective methodology, will enable us to identify more precisely the value of each of the components that traditionally are included in a multi-component intervention aimed to prevent obesity. Developing countries are lacking information on interventions that are effective in the prevention of non-communicable diseases. Studies of this kind should be able to provide the scientific community and public health entities with tools that are both efficacious and evidence-based.

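### Active Breaks schools also receive the activity-related web content, so the averaged factorial effects on MVPA and sedentary time mix the two components

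*Protocol article*

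**What the plan says.** Under Study design, the trial has "four arms defined by a factorial structure of the two components of the intervention", each component being present or absent. The AB-only arm is therefore coded as having no virtual component.

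The description of Active Breaks, under The intervention, says otherwise: "This school-based intervention is complemented with a partial version of the web-based program". On what that version contains: "Its content dealt with the benefits of being physically active, tips on how to reduce screen time, statistics regarding sedentary behaviour", followed by recommended activity for a child and barriers to it.

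The same section gives V two aims. The second includes "increasing mothers’ knowledge of the benefits of PA and consequences of sedentary behaviour". Table 1 lists a physical activity theme of 4 presentations out of 23, described as "Importance of being physically active, recommendations, barriers, and tips for implementation".

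The primary outcomes, listed at the end of Environmental measures, are the child's daily minutes of MVPA and of sedentary time. Statistical considerations bases power on the V and AB main effects and their interaction. It then specifies a mixed model with terms for AB, V, AB + V, time and their time interactions, and says that the most parsimonious model will be reported. The Discussion presents the design as one in which the "components are split off and each one of them is evaluated both separately and then together".

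**The concern.** A factorial main effect isolates a component only if that component is absent wherever its factor is coded "no". Here the part of the web programme aimed at activity and sedentary behaviour is present in the AB-only schools, which are coded V = no. The overlap falls on the content most relevant to the two primary outcomes, and nothing in the article corrects for it or redefines the AB effect.

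The interpretation of the primary results is at stake. The V main effect would be understated, the AB main effect would be credited with part of a web effect, and a negative interaction would appear that says nothing about how breaks and web content work together. A policy reader could attribute to instructor-led breaks a gain produced by web content.

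**Working it through.** **Inputs from Statistical considerations.** N = 160 (40 per arm), Cohen's f = 0.22, F test at α = 0.05, within-cell SD 11 min/day for MVPA and 12 for sedentary time. There are 12 schools in four arms, so 12/4 = 3 per arm if the split is equal.

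**The plan's own figure.** With 1 and 156 degrees of freedom, λ = N·f² = 160 × 0.22² = 7.744. The noncentral F gives power 0.790 (normal approximation 0.795), so the stated 80% reproduces within rounding. The matching difference is 2 × 0.22 × 11 = 4.84 min/day of MVPA, or 2 × 0.22 × 12 = 5.28 min/day of sedentary time. The article rounds these to 5 and 5.4, for which 5/22 = 0.227 and 5.4/24 = 0.225.

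**Arm means.** Take additive effects: b for breaks, p for the shared activity web content, h for the rest of V.

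- C = 0
- V = p + h
- AB = b + p
- AB+V = b + p + h

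**Factorial effects.**

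- V main effect = ½[(V − C) + ((AB+V) − AB)] = ½[(p + h) + h] = h + p/2. Intended: h + p.
- AB main effect = ½[(AB − C) + ((AB+V) − V)] = ½[(b + p) + b] = b + p/2. Intended: b.
- Interaction = (AB+V) − AB − V + C = −p. Intended: 0.

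**Size over an assumed range.** Fix p + h = 4.84 and b = 4.84 min/day, and let s be the share of the V effect carried by the shared content. The article does not give s. The V main effect is 4.84(1 − s/2), with λ = 7.744(1 − s/2)². For the interaction, λ = 160(p/44)².

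| s | V main effect (power) | AB main effect (power) | Interaction (power) |
|---|---|---|---|
| 0% | 4.84 (79%) | 4.84 (79%) | 0 (5%) |
| 25% | 4.24 (68%) | 5.45 (88%) | −1.21 (6%) |
| 50% | 3.63 (55%) | 6.05 (93%) | −2.42 (11%) |
| 75% | 3.03 (41%) | 6.66 (97%) | −3.63 (18%) |
| 100% | 2.42 (28%) | 7.26 (99%) | −4.84 (28%) |

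Effects are in min/day of MVPA. The powers are the same for sedentary time at 5.28 min/day and SD 12, because f is the same. Clustering is ignored, as in the plan's own calculation.

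The last column matters for the parsimony rule. The induced interaction would be detected at most 28% of the time in this range, so a selection step could easily drop the term and leave only the mixed main effects.

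**If breaks do nothing.** With b = 0 and p = 4.84, AB minus C is still 4.84 min/day (rejected about 50% of the time) and the AB main effect is 2.42 (about 28%).

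**Contrasts that stay interpretable.** V − C = p + h, the full web effect. (AB+V) − V = b, breaks given full web content, provided AB+V families get no activity content beyond V's. Each compares 40 with 40 children: λ = 4.84²/(2 × 11²/40) = 23.43/6.05 = 3.87, which gives about 50% power. Reaching 80% would take about 82 children per arm.

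**The case against.** A reader might infer that the trial cannot separate the components at all. The document does not support that. The planned model has terms for AB, V and AB + V, each with time, and so can fit all four arms. V minus C and (AB+V) minus V are linear combinations of its time interactions. The mixing affects the averaged main effects and the interaction on which power is based, and AB minus C. The reservation is the parsimony rule, which could remove the term that these contrasts need.

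A reader might also take the fall in V power to about 28% as the expected loss. It is the extreme case, in which the shared content carries all of V's effect. The article does not say that the partial version equals the four physical activity presentations. V also proposes enjoyable movement activities for children and covers parents as role models and energy balance, none of which is in the partial version as described.

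Nor does it follow that the main effects should be replaced. A simple contrast has a standard error √2 times that of the main effect, so the diluted V main effect still has more power whenever 1 − s/2 > 0.707, that is, when s is below about 0.59.

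Finally, AB can be read as a package that includes its web content, and comparing packages is legitimate. That stands for AB minus C, which equals b + p. It does not rescue the AB main effect: b + p/2 is the effect of neither the package nor the breaks. It also does not fit the Discussion's claim, or the statement under The intervention that knowledge and education are delivered by the virtual component.

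**Conclusion.** The point holds for the averaged factorial effects on MVPA and sedentary time. For any p above zero, V is understated by p/2, AB is overstated by p/2, and the interaction is shifted by −p. This contradicts the claim of separate evaluation. The algebra assumes additive effects and a partial version that works equally well in AB schools and within full V. The size is unknown: nominal V power runs from 79% with no overlap to 28% with complete overlap, before clustering. Randomisation is not affected, and V versus C and AB+V versus C remain valid comparisons of what was delivered. The effect of breaks without any web content can be estimated only by assuming additivity. Diet outcomes are little affected, because the partial version as described carries no diet content.

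**What to change.** 1. Label the AB component as active breaks plus activity web content throughout, and reconcile this with the yes/no coding under Study design.
2. Withdraw the claim that the AB and V main effects isolate each component on activity outcomes.
3. For MVPA and sedentary time, keep the AB × V interaction with time in the model whatever the parsimony rule would select.
4. From that model, report V minus C and (AB+V) minus V alongside the factorial effects. State whether AB+V families get any activity content beyond V's, since the second contrast depends on it.
5. State that these contrasts rest on 3 versus 3 schools and 40 versus 40 children, with about 50% power at 4.84 min/day before clustering, and that breaks without web content are not estimated directly.
6. Keep the factorial main effects for diet outcomes.

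The changes concern analysis and wording, with no new data. The cost is precision: the interpretable contrasts are noisier than a valid main effect would have been, so the activity conclusions on each component will be more cautious.
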